**Neuropsychological assessment**				
*Global cognition*				
Mini Mental State Examination (MMSE)	x	x	x	x
Montreal Cognitive Assessment (MoCA)	x	x	x	x
*Episodic long-term memory*				
Logical Memory Test immediate and delayed recall	x	x	x	x
Rey’s 15 words test immediate and delayed recall	x	x	x	x
Rey Complex Figure delayed recall	x	x	x	x
*Logical-executive functions*				
Rey Complex Figure copy	x	x	x	x
Raven’s Matrices 1947	x	x	x	x
Frontal Assessment Battery (FAB)	x	x	x	x
Semantic fluency	x	x	x	x
Phonological fluency (FAS)	x	x	x	x
*Working memory*				
Digit Span (forward/backward)	x	x	x	x
Corsi’s block-tapping test span (forward/backward)	x	x	x	x
*Attention/processing speed*				
Attentive Matrices	x	x	x	x
Trail Making Test A and B (TMT)	x	x	x	x
**Questionnaires and scales**				
*Functional level*				
Activities of Daily Living (ADL)	x			x
Instrumental Activities of Daily Living (IADL)	x			x
*Depressive symptoms*				
Beck Depression Inventory (BDI)	x	x	x	x
*Health status*				
12-Item Short Form Health Survey questionnaire (SF-12)	x	x	x	x
*Cognitive reserve*				
Cognitive Reserve Index questionnaire (CRIq)	x			
*Caregiver distress*				
Zarit Burden Inventory (ZBI)	x	x		
**Participant-centered outcomes**				
*Impression of symptom change*				
Patient Global Impression of Change (PGIC)		x		
*Treatment adherence*				
Number of sessions carried out		x		

T0 = baseline assessment; T1 = post-intervention assessment; T2 = 6-month follow up; T3 = 12-month follow up.

### Data management

Study data will be recorded in the REDCap database in compliance with the General Data Protection Regulation (GDPR). All participants will be registered with an identification code. The database will be kept updated to reflect the participant’s status at each stage during the course of the study. The collected data, after scientific publication, will be deposited in dedicated repositories according to the good practice of data sharing.

### Participants and eligibility criteria

Participants will be recruited from the Cognitive Disorders and Dementia Centre outpatient services and Movement Disorders and Neurorehabilitation Unit of IRCCS Mondino Foundation (Pavia, Italy), from the Unit of Neurology, University-Hospital of Parma (Parma, Italy), from the Neurological Clinic and NEUROMET of the IRCCS Institute of Neurological Sciences of Bologna-University of Bologna and the IRCCS S. Lucia Foundation of Rome. These patients will be asked to participate as volunteers in the study. Following their consent, they will be screened for eligibility criteria through a clinician evaluation carried out by an expert neurologist.

The inclusion criteria for participants will be:

Diagnosis of amnestic MCI (Petersen et al., 1999) or Parkinson’s disease with MCI (Litvan et al., 2011);Aged between 60 and 85 years;Years of education ≥5;Clinical Dementia Rating (CDR) (Hughes et al., 1982) score = 0.5.The exclusion criteria will be:Mini-Mental State Examination (MMSE) score < 20;Presence of cognitive impairment secondary to an acute or general medical disorder (e.g., brain trauma, small vessel disease, vascular impairment or tumor);Presence of severe neuropsychiatric conditions (e.g., mood and behavioral disorders);Presence of severe sensory disorder (e.g., deafness or blindness) or motor impairments that prevent trunk control and/or sitting position;Current cognitive treatments;Lack of family support.

### Participants’ evaluation

See Table 1 for the evaluation battery (neuropsychological assessment, questionnaires and scales, and participant-centered outcomes) across testing sessions. Each evaluating session will be about 90 min per participant and will be carried out in a hospital setting.

### Neuropsychological assessment

The cognitive assessment, performed by using neuropsychological tests standardized for the Italian population, will evaluate the following cognitive domains:

Global cognitionMini Mental State Examination (MMSE) (Magni et al., 1996);Montreal Overall Cognitive Assessment (MoCA) (Conti et al., 2015);Episodic long-term memoryLogical Memory Test for immediate and delayed recall (Novelli et al., 1986; Spinnler, 1987)Rey’s 15 words test for immediate and delayed recall (Carlesimo et al., 1996);Rey Complex Figure delayed recall (Caffarra et al., 2002);Logical-executive functionsRaven’s Matrices 1947 (Carlesimo et al., 1996);Frontal Assessment Battery (Appollonio et al., 2005);Semantic fluency (Novelli et al., 1986);Phonological fluency (FAS) (Carlesimo et al., 1996);Visuo-constructive functionsRey Complex Figure copy (Caffarra et al., 2002);Working memoryDigit Span (Forward/Backward) (Monaco et al., 2013);Corsi’s block-tapping test span (Forward/Backward) (Monaco et al., 2013);Attention/processing speedDigit Cancellation Test (Spinnler, 1987);Trail Making Test A and B (Giovagnoli et al., 1996).Parallel forms (i.e., alternative versions using similar material) will be applied for follow-up visits when available in order to avoid possible learning effect. All test scores will be corrected for age, sex, and education by using appropriate correction grids and compared with the values available for the Italian population.

### Questionnaires and scales

Additionally, we will administer the questionnaires and scales reported below to evaluate the following aspects:

Functional levelActivities of Daily Living (ADL) (Lawton and Brody, 1969);Instrumental Activities of Daily Living (IADL) (Lawton and Brody, 1969);Depressive symptomsBeck Depression Inventory (BDI) (Beck et al., 1996);Health status12-Item Short Form Health Survey questionnaire (SF-12)4 (Ware et al., 1996)Cognitive reserveCognitive Reserve Index questionnaire (CRIq) (Nucci et al., 2012);Caregiver distressZarit Burden Inventory (ZBI) (Nucci et al., 2012).

### Participant-centered outcomes for monitoring adherence to TR interventions

In order to assess the subjective evaluation of TR success, we will evaluate the following aspects at T1: (a) Impression of symptom change through the Patient Global Impression of Change (PGIC) (Hurst and Bolton, 2004). (b) Treatment adherence considering the number of sessions carried out by the patient. To monitor and report adherence accurately, we will implement several strategies.

We will use digital tracking tools integrated into the TR platform to log each session automatically. These tools will record the duration and completion status of each session, providing real-time data on patient adherence. Additionally, patients will complete adherence logs, which will be cross-referenced with the digital records to ensure accuracy.

To manage deviations from the planned protocol, we will establish predefined criteria for non-adherence (e.g., missing a specified number of sessions) and implement a follow-up protocol. This protocol will include automated reminders sent via email to encourage session completion and regular check-ins by a designated adherence coordinator who will contact patients directly to address any barriers to adherence and provide support.

Non-adherence will be documented, and reasons for missed sessions will be categorized (e.g., technical issues, personal reasons) to identify common obstacles and improve the TR program. Adherence data will be reported in both aggregate and individual formats, highlighting overall adherence rates, trends over time, and any significant deviations from the protocol. This detailed reporting will allow us to evaluate the effectiveness of our adherence strategies and make necessary adjustments to enhance patient engagement.

By implementing these comprehensive monitoring and management strategies, we aim to ensure high adherence rates and the successful delivery of the telerehabilitation interventions.

In order to assess subjective evaluation of TR success, we will evaluate the following aspects at T1: (a) Impression of symptom change through the Patient Global Impression of Change (PGIC) (Hurst and Bolton, 2004). (b) Treatment adherence considering the number of sessions carried out by the patient.

### Brain resting state connectivity measures

#### Rs-fMRI functional connectivity

Each center is equipped with a high field MRI scanner (i.e., GE or Siemens 3 T). A harmonized MRI protocol, already developed by the Neuroscience and Neurorehabilitation Network (RIN), the Italian largest research network in the neuroscience field, will be used. The protocol will include the following sequences: 3D T1 weighted images (3D T1w), 3D T2 weighted Fluid Attenuated Inversion Recovery (3D T2-FLAIR) images and resting-state functional magnetic resonance imaging (rs-fMRI).

Structural MRI images will be acquired using a 3D MPRAGE T1-weighted sequence with the following parameters: TR = 2,300 ms; TE = 2.98 ms; TI = 900 ms; flip angle = 9°; voxel size = 1.1 × 1.1 × 1.2 mm^3^; Field of view = 256 × 240 mm^2^; 170 slices. Resting-state fMRI images will be acquired with eyes closed using a T2-weighted echo-planar imaging sequence with the following parameters: TR = 3,000 ms; TE = 30 ms; flip angle = 80°; 48 slices of 3.3 mm; 140 volumes; acquisition duration ~10 min. Structural and functional MRI data will be pre-processed and analyzed using SPM12 (Wellcome Centre for Human Neuroimaging, London, United Kingdom) and the CONN toolbox. The following pre-processing steps will be applied: (1) slice-timing and realignment; (2) co-registration of structural and functional images; (3) segmentation of T1-weighted images into gray matter (GM), white matter (WM) and cerebrospinal fluid (CSF) tissue maps; (4) normalization of both T1- and T2*-weighted scans into the MNI space; and (5) smoothing of both images via a Gaussian kernel of 6 mm. Multiple denoising steps will be carried out on pre-processed T2*-weighted images: (1) regressing out the first 5 components of WM and CSF signal; (2) regressing out motion parameters; (3) application of a band-pass filter (0.008–0.1 Hz) to remove non-neural signals; (4) linear detrending; and (5) de-spiking. GM, WM and CSF volumes will be extracted and summed to calculate total intracranial volume for each participant to be used as a covariate in the analyses.

Seed-based analysis will be conducted on each patient’s rs-fMRI acquisitions to determine the pairwise correlation between the hemodynamic signals extracted from seed regions and the whole-brain signals at voxel level. The resulting maps are typically interpreted as representing the functional connectivity of those seed regions (Smith et al., 2014).

#### HD-EEG synchronous activity

HD-EEG will be acquired in the different centers following the same procedure. In details, signals will be acquired for 12 min (6 min eyes open and 6 min eyes closed) at a sampling frequency of 1,000 Hz. For HD-EEG recording, a HydroCel Geodesic Sensor NetTM cap will be utilized. The pre-wired cap allows for the correct placement of 128 electrodes with approximate inter-electrode distances of 20–25 mm. HD-EEG pre-processing and source localization: The HD-EEG will be recorded with a Notch filter centered at 50 Hz to eliminate related artifacts. EEG signals will be filtered (1–80 Hz) with a zero-phase distortion FIR filter and downsampled to 250 Hz. Biologically originated artifacts will be discarded using independent component analysis. An anatomical head model has been utilized, identifying 12 different tissue classes (skin, eyes, muscles, fat, spongy bone, compact bone, gray matter, cerebellar gray matter, white matter, cerebellar white matter, cerebrospinal fluid, and brainstem). Source reconstruction will be performed using exact Low-Resolution Brain Electromagnetic Tomography (eLORETA). After cortical source reconstruction using the LORETA method, different frequencies will be decomposed using the Fourier transform as a mathematical operator.

Brain connectivity will be investigated across all frequency bands using a seed-based technique, calculating connectivity between each seed and all other brain voxels. A 2-s Hamming window, with 50% overlap between consecutive windows, will be used to reconstruct frequencies ranging from 1 to 80 Hz. EEG connectivity maps will be created by estimating the Pearson’s correlation coefficient between each seed time series using a standard MATLAB^®^-based code.

### Outcome measures

#### Primary outcome measures

Our primary goal is to understand how TR may affect RSNs communications in participants diagnosed with MCI due to a neurodegenerative disease. Primary outcomes will be measured through the assessment of changes in resting-state brain connectivity obtained from HD-EEG and rs-fMRI techniques. This would enable monitoring variations in resting-state connectivity involved during rehabilitative activities. Resting-state brain connectivity plays a critical role in deactivation during specific tasks, but this process becomes compromised with aging and progression toward neurodegenerative diseases. Consequently, interventions aimed at restoring brain connectivity have the potential to provide cognitive benefits in the early stages of the disease.

We plan to assess rs-fMRI FC and/or HD-EEG SA at two time points: before the TR (T0) and within 2 weeks of TR completion (T1). All the obtained measures will be compared with the results obtained from the MCI participants assigned to the control groups.

#### Secondary outcome measures

As the secondary outcome measures, we will consider the longitudinal changes in all the neuropsychological tests, questionnaires, and scales (T1, T2, and T3 vs. T0 when applicable according to Table 1). Secondary outcome measures will also include participant-centered outcomes to assess those aspects that are most important for the participants and the subjective evaluation of intervention success at T1. We will also correlate these findings with changes in FC/SA between T0 and T1. Furthermore, we will evaluate caregiver burden at different time points.

### Planned analysis

#### Primary outcome analysis plan

Brain connectivity measures will be extracted from both rs-fMRI and HD-EEG data. The RSNs will be constructed considering a predetermined set of seed regions (Franco et al., 2013). As we will, for the first time, investigate the efficacy of three distinct TR approaches and their associated neural correlates, we will examine brain connectivity across all major RSNs.

For rs-fMRI seed-based timecourses will be extracted from each seed region, and individual maps of functional connectivity will be computed modeling the linear association between the timecourse of the seed and the timecourse of each voxel within the identified RSNs. For HD-EEG data, brain connectivity will be extracted by assessing the weighted Phase Lag Index (wPLI) (Vinck et al., 2011) that measures the phase synchronization of two signals. For both methods, the strength of the relationship between nodes of RSNs will be quantified using seed-based analysis, estimating pairwise correlations between a seed region and all the other voxels across the brain.

We will assess if the TR intervention has effects on changes in functional connectivity between T0 and T1 and whether these effects are absent at T0 vs. T1 in the control stimulation. This approach enhances the validity of the analyses by specifically addressing the impact of the treatment on connectivity changes over time and comparing them with a control condition.

Using the formula (Δ connectivity change = T1 − T0), the changes in Pearson’s correlation coefficient transformed into z-scores will be computed for each participant within each network. A large Δ connectivity change will represent a higher correlation coefficient (stronger connectivity) at T1 than T0.

The effect of the cognitive training program on network connectivity will be tested using mixed-design full-factorial scripts modeling the condition-by-timepoint interaction (increases Δ connectivity change seen in the experimental condition net of the increases seen in the control condition). We will also test the “inverse interaction” contrast (exclusive increases in Δ connectivity change seen in the control condition) as a methodological control. The statistical model will be run independently for each considered TR approach (i.e., NBCT, HomeCoRe, and SMRT).

To account for the nested data structures (e.g., patients nested within different centers), we will employ multilevel modeling (MLM). MLM will allow us to partition the variance at different levels (e.g., within-patient, between-patient, and between-center) and accurately estimate the effects of the cognitive training program while accounting for potential clustering. This approach will help in managing the hierarchical nature of the data, improving the precision of our estimates.

Potential confounding variables (center of acquisition, MCI subtype, age, sex, functional activities, current pharmacological treatment, cognitive reserve) will be considered as covariates.

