Outcome measures	Primary outcome: Assessment of resting-state functional connectivity at baseline (T0) and at the end of NBCT (T1 after 4 weeks). Secondary outcome: Global cognitive and neuropsychological changes at T1, T2, and T3 vs. T0 when applicable according to Table 1. Secondary outcome measures will also include participant-centered assessment at T1.	Primary outcome: Assessment of resting-state functional connectivity at baseline (T0) and at the end of HomeCoRe (T1 after 6 weeks). Secondary outcome: Global cognitive and neuropsychological changes at T1, T2, and T3 vs. T0 when applicable according to Table 1. Secondary outcome measures will also include participant-centered assessment at T1.	Primary outcome: Assessment of resting-state functional connectivity at baseline (T0) and at the end of SMRT (T1 after 6 weeks). Secondary outcome: Global cognitive and neuropsychological changes at T1, T2, and T3 vs. T0 when applicable according to Table 1. Secondary outcome measures will also include participant-centered assessment at T1.	Primary outcome: Assessment of resting-state functional connectivity at baseline (T0) and at the end of sham intervention (T1 after 4 or 6 weeks). Secondary outcome: Global cognitive and neuropsychological changes at T1, T2, and T3 vs. T0 when applicable according to Table 1. Secondary outcome measures will also include participant-centered assessment at T1.

The primary active condition involves administering the NBCT protocol to 40 subjects with MCI across all included centers. The HomeCoRe protocol, involving 5 subjects, will be conducted exclusively in Pavia, while the SMRT protocol, involving 10 subjects, will be implemented only in Rome. The control condition consists in an unstructured home-based cognitive stimulation, involving 60 min of daily activities, with MCI sample size, frequency and overall treatment duration adapted to the experimental treatment of comparison. For each session, newspaper articles will be provided for the patient to read and summarize in a diary by answering specific questions. The protocol is administered remotely through TR with online assistance from a therapist.

Each patient will undergo brain rs-fMRI or HD-EEG acquisitions before (T0) and after (T1) active or control interventions.

Follow-up in-person neuropsychological assessments will be scheduled within 2 weeks from the end of the rehabilitation program (T1), and after 6 (T2) and 12 months (T3).

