### Power analysis

In line with the findings from De Marco et al. (2017), where increased DMN resting-state connectivity was observed in patients assigned to the experimental condition in a midline cluster extending to the precuneus and cuneus, we aim to detect similar changes in brain functional connectivity through our study. De Marco et al. reported decreased connectivity in the right and left parietal cortices for the control condition. The experimental condition showed an average increase of 0.18 z scores, while the control condition exhibited an average decrease of 0.63 z scores (mixed-design ANOVA’s F1, 35 = 15.08, *p* < 0.001). Based on these findings, we conducted a power analysis to determine the necessary sample size for detecting differences in functional connectivity changes between the experimental and control groups. Assuming a medium effect size (Cohen’s *d* = 0.5), a significance level of 0.05, and a power of 0.90, our analysis indicated that a total sample size of approximately 80 participants (40 per condition, evaluated at two time points for NBCT) would be sufficient to detect medium to large effects, ensuring robust and reliable results.

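### The primary outcome is a family of connectivity changes (all major networks, two modalities) with no measure named as primary, while the power analysis sizes a single contrast in all 80 NBCT participants

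*Protocol article*

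**What the plan says.** **Outcome.** Primary outcome measures defines the primary outcome as change in resting-state connectivity from T0 to T1, obtained with HD-EEG and rs-fMRI. The Primary outcome analysis plan computes one change score per participant in each network and states "we will examine brain connectivity across all major RSNs". The model is run separately for NBCT, HomeCoRe and SMRT. The HD-EEG section adds that connectivity is examined in all frequency bands. No network, seed, band or modality is singled out.

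**Modality.** Study design says "Each patient will undergo brain rs-fMRI or HD-EEG acquisitions before (T0) and after (T1) active or control interventions", and the Abstract has the same either-or wording. Primary outcome measures says "We plan to assess rs-fMRI FC and/or HD-EEG SA at two time points". The Primary outcome analysis plan says "Brain connectivity measures will be extracted from both rs-fMRI and HD-EEG data". The rs-fMRI section says "Each center is equipped with a high field MRI scanner".

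**Sample size.** The Power analysis starts from an earlier study in which "increased DMN resting-state connectivity was observed in patients assigned to the experimental condition". It then proceeds "Assuming a medium effect size" (d = 0.5), with "a significance level of 0.05, and a power of 0.90", and arrives at about 80 participants, 40 per condition, for NBCT. It names no modality. It makes no allowance for several networks, or for participants who have only one of the two modalities.

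**The concern.** A power statement refers to a particular test: one outcome, one alpha and one number of participants. Here the outcome section defines many tests of equal standing and the power section describes one. If the family is tested with control of the overall error rate, each test has a smaller alpha and less power than stated. If it is tested without control, a positive finding in one network or band carries less evidence than a 0.05 threshold suggests.

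The modality wording adds a second gap. EEG phase synchrony (the weighted phase lag index) and the rs-fMRI time-course association are different quantities, and the plan gives each its own metric. The number per arm in a primary test is therefore the number with that modality. The article does not settle whether that is 40.

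The article aims to establish efficacy and describes its sample size as giving robust and reliable results. Those claims need an identifiable primary test.

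**Working it through.** **Inputs from the Power analysis:** d = 0.5, alpha 0.05 (sidedness not stated; two-sided taken), power 0.90, 40 per arm.

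**Assumptions, not in the article:** K = 7 to 10 major networks; a common correlation of 0.5 between test statistics as an alternative to independence; an even split between modalities (20 per arm).

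**1. The plan's own figure.** Two-sample comparison of change scores:

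n per arm = 2(1.960 + 1.282)² / 0.5² = 2 × 10.51 / 0.25 = 84.1, so 85 per arm (86 by the t distribution), or about 170 in total.

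The stated 80 is not reproduced. With 40 per arm, the noncentrality is 0.5 × √(40/2) = 2.236 and the critical t on 78 df is 1.991, so power is 0.60. One-sided testing raises this to 0.72. A repeated-measures interaction with f = 0.25 gives 82 or 78 in total, but only if the T0–T1 correlation is 0.05 or 0.10, which is not stated. This is a separate error. It matters here because 60%, not 90%, is the proper baseline for the comparisons below.

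**2. Familywise error if each network is tested at 0.05 without correction.** Under independence it is 1 − 0.95^K. The last column is the same quantity for equicorrelated normal statistics.

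| K | Independent | Common correlation 0.5 |
|---|---|---|
| 7 | 1 − 0.95^7 = 0.30 | 0.23 |
| 10 | 1 − 0.95^10 = 0.40 | 0.29 |

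These are for one modality and one treatment approach. EEG bands and the second modality would add to them. The inverse contrast is not counted.

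**3. Power if the family is corrected.** Bonferroni at K = 7 gives alpha = 0.05/7 = 0.0071. With 40 per arm the critical t is 2.763 and the noncentrality is still 2.236, so power is 0.31, against 0.60 for one test. To reach 90% at that alpha would need 127 per arm (normal approximation).

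The mismatch remains even if the sizing error is set aside. Taking d = 0.735, at which 40 per arm does give about 90% for one test, Bonferroni for 7 networks gives 0.70.

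**4. Power if each participant has one modality and the split is even.** With 20 per arm and d = 0.5, the noncentrality is 0.5 × √(20/2) = 1.581 and the critical t on 38 df is 2.024, so power is 0.34 for one uncorrected test. The loss due to the split is from 0.60 to 0.34. A 90% power would need d = 1.05.

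**5. The modality passages side by side.** The Abstract and Study design give each patient one or the other. Primary outcome measures allows one or both. These two conflict. The analysis section's reference to both can be read as describing the data sources across the study, so it fits either rule.

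**The case against.** **Correction may be specified elsewhere.** An article commonly leaves the multiplicity method (voxel or cluster thresholds, false discovery rate, alpha split) to the full protocol or SAP. This stands: the missing correction method is not the fault. A reader might infer that any network in either modality may be declared the primary success and that the type I error is far above 5%. The article states no such success rule and does not exclude correction, so the 30–40% is an upper illustration. What remains is inside the article: the outcome it defines is not the test it sized.

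**All 80 might have rs-fMRI.** Under the and/or wording, with a scanner at every centre, that is possible. A reader might infer that every primary test runs in fewer than 80. That follows only if participants have one modality each and it differs between them. The 50:50 split is an assumption.

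**What the power section fixes.** It might be read as sizing a posterior-DMN rs-fMRI endpoint. The text cites a DMN result as motivation, then uses a generic d = 0.5 and names no modality, so that reading is not supported.

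**Pooling and the inverse contrast.** Nothing in the article plans to pool modalities, and the inverse contrast is labelled a methodological control. Neither adds to the problem.

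**Exploratory intent.** The Discussion looks ahead to larger confirmatory trials, and the analysis plan justifies its breadth as a first investigation. But the same article claims efficacy aims and 90% power, so the mismatch still has to be resolved.

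**Conclusion.** The point holds in this form: the primary outcome is a family with no designated measure, the sample size is for one contrast in all 80 NBCT participants, and the stated 90% power does not describe the primary analysis as defined. That, and the conflict between the either-or and the and/or wording, rest on the text alone.

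The sizes rest on assumptions. For 7 to 10 networks without correction, familywise error is at most about 30–40%, and about 23–29% at a correlation of 0.5. Bonferroni for 7 networks takes power from about 60% to about 31% at d = 0.5. An even modality split takes it from about 60% to about 34% for one test. The fall from 90% to 60% belongs to the separate sample-size error and should not be charged to this point.

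**What to change.** 1. Name one primary measure for NBCT versus its control at T1: network or seed, modality, and band if EEG. The DMN is the natural choice given the Power analysis; the modality is for the sponsor to decide. Alternatively, keep the family and state the alpha rule that governs it.
2. Make the remaining networks, bands and the other modality secondary.
3. Reconcile the Abstract and Study design with Primary outcome measures on which participants have which modality at T0 and T1.
4. Restate the power at the number per arm expected to have the primary modality and at the alpha actually used.

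**Cost.** If current acquisition plans already provide the chosen modality, this is a change of wording. If they do not, either acquisition changes or participants without that modality drop out of the primary test. The other networks and the other modality lose primary status, and the stated power will fall.

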### Control for confounding variables and biases

After baseline assessment, patients included in the study will be randomly allocated to two groups in a ratio of 1:1 based on active and control interventions, controlling for sex and education levels. We will generate random numbers with a computer algorithm^1^ from a uniform distribution in the range 0–1, dividing the range into two equal intervals and assigning each participant to the group corresponding to the sampled number (1,1 ratio). Stratification will be employed to ensure equal distribution of participants within each stratum (e.g., blocks based on sex and education level), and block randomization will be used within each block. Propensity score matching will be applied using logistic regression and matching participants based on similar scores, to ensure comparable groups.

Neuropsychologists carrying out cognitive evaluations will be blinded to group allocation to prevent bias. They will receive appropriate instruction and guidance regarding all assessment procedures and outcome parameters. Reminders (e.g., written reminders, phone calls, and email messages) for each visit will be sent to all participants to ensure compliance and complete data collection.

Not all outcome measures will be administered at each time point (summary in Table 2).

**Table 2 tab2:** Evaluation battery across testing sessions.

	T0	T1	T2	T3

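### The primary analysis of connectivity change adjusts for neither baseline connectivity nor education, a stratification factor, and gives centre two roles: unbiased, but inefficient and loosely specified

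*Protocol article*

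**What the plan says.** All references are to the protocol article.

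- **Response and test.** 'Primary outcome analysis plan' defines a change score, T1 minus T0, per participant and network. It then tests the training effect with "mixed-design full-factorial scripts modeling the condition-by-timepoint interaction", explained in brackets as the experimental increase in that change net of the control increase. The Abstract also says effects are tested on the change. The same section asks "whether these effects are absent at T0 vs. T1 in the control stimulation". The model is run separately for NBCT, HomeCoRe and SMRT.
- **Multilevel structure.** The section adds: "MLM will allow us to partition the variance at different levels (e.g., within-patient, between-patient, and between-center".
- **Covariates.** "Potential confounding variables (center of acquisition, MCI subtype, age, sex, functional activities, current pharmacological treatment, cognitive reserve) will be considered as covariates".
- **Randomisation.** 'Control for confounding variables and biases' allocates patients "in a ratio of 1:1 based on active and control interventions, controlling for sex and education levels", with blocks within these strata.
- **Centres.** 'Study design' names four centres. NBCT runs in all of them, HomeCoRe only in Pavia (5 active, 5 control) and SMRT only in Rome (10 and 10).
- **Sample size.** 'Power analysis' assumes d = 0.5 with "a significance level of 0.05, and a power of 0.90" and arrives at about 40 per condition for NBCT.

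**The concern.** Four features of the primary model are fixed badly.

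1. T0 connectivity is measured in every participant but does not appear among the covariates, so precision is given away.
2. Education is a stratification factor but is not in the list, while sex is in both places.
3. Centre is given two roles that do not sit together, and in two of the three models it does not vary.
4. The response is described as the change in one sentence and as a factor crossed with timepoint in the next. The within-patient variance mentioned later exists only if T0 and T1 are separate responses.

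What is at stake is power in a comparison with 40 per arm, and a primary model that two analysts would write down in the same way.

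**Working it through.** **Inputs.** Alpha 0.05, power 0.90, d = 0.5 and 40 per arm come from 'Power analysis'. Sidedness is not stated; two-sided is assumed. Nor does the article say whether d is in SDs of the change or of a single visit, so both are shown. The T0-T1 correlation r is not given; 0.3 to 0.7 is assumed, with equal SD at both visits.

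**1. The plan's own figure.** For a two-sided comparison of two means, n per arm = 2(1.960 + 1.282)²/0.5² = 84.1, so 85 (86 by the t distribution). Power at 40 per arm is 0.61 (0.60 by t). One-sided, the figures are 69 per arm and 0.72. A total near 80 appears only under unstated assumptions: a within-between interaction with f = 0.25 and r about 0.05 to 0.10, or a single-visit d = 0.5 with r about 0.76. That mismatch is a separate matter. It is used here only as the starting point.

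**2. Interaction versus change.** The interaction contrast is (E1 − E0) − (C1 − C0), where E and C are arm means and 0 and 1 are the visits. That equals mean change in E minus mean change in C. In one simulated data set of 40 versus 40, the interaction F was 1.1159 and the squared t for the change was 1.1159. Either reading of the plan is therefore a comparison of raw change, with no adjustment for T0.

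**3. Cost of not adjusting.** With single-visit SD s:

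- variance of the change = 2(1 − r)s²
- variance of T1 given T0 = (1 − r²)s²
- ratio = (1 − r²)/[2(1 − r)] = (1 + r)/2

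| r | Variance ratio | d on change scale: power at 40/arm, raw to adjusted | n/arm for 0.90, raw to adjusted | d on single-visit scale: power at 40/arm, raw to adjusted |
|---|---|---|---|---|
| 0.3 | 0.65 | 0.61 to 0.79 | 85 to 55 | 0.46 to 0.64 |
| 0.5 | 0.75 | 0.61 to 0.73 | 85 to 64 | 0.60 to 0.72 |
| 0.7 | 0.85 | 0.61 to 0.68 | 85 to 72 | 0.81 to 0.87 |

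Change-scale entries use the normal approximation. For r = 0.3, 0.5/√(2/40) = 2.236; 2.236/√0.65 = 2.773; 2.773 − 1.960 = 0.813, which gives 0.79. Single-visit power uses the t distribution with d = 0.5/√(2(1 − r)) before adjustment and 0.5/√(1 − r²) after. The normal approximation gives values about 0.01 higher.

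**4. Education.** The stratification factors are sex and education. The covariate list contains sex, age, MCI subtype, functional activities, drug treatment, cognitive reserve and centre. Education is missing, and nothing says that cognitive reserve replaces it. Where education predicts the connectivity outcome, stratified allocation removes that variation from the between-arm difference, but a model without education leaves it in the residual. The standard error is then too large.

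**5. Centre.** If the covariate is a set of fixed centre effects, these absorb all differences between centres and no between-centre variance is left to estimate. If centre is only a random level, four centres estimate that variance poorly. In the HomeCoRe and SMRT models, taking their control groups to be at the same single centre, centre is constant and neither term can be estimated.

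**6. Response.** With the change as response there is one value per participant and network, so there is no timepoint factor and no separate within-patient variance. With T0 and T1 as responses, both exist. The text supports either reading.

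**The case against.** The strongest reply is that nothing here is invalid. Under randomisation the raw change comparison is unbiased, and a mixed-design interaction on two visits is a standard analysis. 'Power analysis' speaks of participants evaluated at two time points and takes its effect from a mixed-design ANOVA, which favours the T0/T1 reading. The correlation and the scale of d are assumptions, so the gain is not a figure the documents supply. All of this stands. It makes the point one of efficiency and clarity, not of error in the test.

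Three stronger readings are tempting, and the documents do not support them.

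- *The model cannot be fitted.* This is true only if a timepoint factor is applied to the change score itself. Read as an interaction on T0 and T1 values, the model can be fitted and gives the same test as the change.
- *Leaving out education invalidates the inference.* The standard errors are too large, not too small. The test is conservative and false positives are not inflated.
- *The treatment effect will be judged by the control arm showing no change.* That sentence is a loose statement of aim. The same section names a between-arm interaction, and 'Primary outcome measures' says results will be compared with the control groups. No passage makes within-arm significance the decision rule.

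It can also be said that T0 is already in the model as a response level. That does not recover the precision. A full-factorial model lets the arms differ freely at T0, so its interaction is still the raw change comparison.

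**Conclusion.** The point holds as one of efficiency and specification. The primary comparison is unbiased but forgoes a variance reduction of 35%, 25% or 15% at assumed r of 0.3, 0.5 or 0.7. At 40 per arm this is worth about 0.07 to 0.18 in power if d = 0.5 is on the change scale, and about 0.06 to 0.18 if it is on the single-visit scale. These figures assume equal SD at both visits, a two-sided 0.05 test and complete data. Where other covariates are in the model, r is the correlation given those covariates.

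The omission of education is a plain inconsistency between two lists in the article, with a conservative effect whose size cannot be computed from the documents. The double role of centre is redundant if the covariate is fixed, and it is inestimable in the two single-centre models on any reading. The response variable is ambiguous and should be named.

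**What to change.** For each network measure, state one model: ANCOVA of T1 connectivity on arm, T0 connectivity, sex, education level and the other pre-specified baseline covariates. Enter centre as a fixed effect in the NBCT model only. Drop the random centre level, and use no centre term for HomeCoRe or SMRT. Base inference on the two-sided between-arm contrast with its 95% CI. Say that absence of change within the control arm will not be taken as evidence of a treatment effect.

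Two practical notes:

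- HomeCoRe has 10 participants. An intercept, arm, T0, sex, education and the five other non-centre covariates make 10 parameters even at one each, which leaves no residual degrees of freedom. A shorter list, with T0 connectivity kept first, must be fixed in advance for that model.
- For voxelwise maps, T0 must enter voxel by voxel. Network-level summaries need only one value per network.

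The cost is mainly wording. T0 connectivity is already collected, and education level is needed for stratification. The change does not settle which network or modality is primary; that is a separate matter.
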